#### 2.3.2. Usual Care/Control Group

Participants randomly assigned to the control group (*n* = 13) will receive the usual treatment, which is stipulated by their gynaecologist. Additionally, during the initial evaluation session, the trained physiotherapist assessor will offer general advice about the positive effects of physical activity and a healthy lifestyle for their HRQoL. For ethical reasons, control participants will be given the opportunity to participate in an exercise program with the same characteristics of this therapeutic exercise intervention after completion of this study, although their results will not be included in the analyses.

### 2.4. Outcome Assessment

Baseline, immediately after intervention and long-term evaluation, will be carried out in the CUIDATE unit, a platform for physiotherapy research in oncology and related diseases. Sessions will be conducted by a trained technician from the research group with 5 years of experience in taking these measurements and who will be blinded to patient group. In order to minimize the influence of menstrual cycle variability on study results, outcome assessment will be performed between days 2 and 10 of the menstrual cycle in women who are not using hormonal contraceptives. Table 2 summarizes primary and secondary outcomes that will be assessed, together with the list of validated instruments that will be used during the assessment.

#### 2.4.1. Primary Outcome: Health-Related Quality of Life

HRQoL will be addressed through the Spanish version of the Endometriosis Health Profile-30 (EHP-30) [57,58], a 30-item, disease-specific tool to evaluate HRQoL in women with endometriosis with high reliability (Cronbach’s α ranged between 0.79 and 0.97). It contains a total of five domains (pain, control and powerlessness, emotional well-being, social support and self-image), and items within each domain, answered on a 5-point Likert-type scale, are summed and transformed to a percentage scale. Scoring ranges from 0 to 100, with higher scoring representing a worse health status.

#### 2.4.2. Secondary Outcomes

Pain

Algometry will be used to measure PPT [59] levels in abdomen, pelvis and lower back regions based on previously published protocols for the evaluation of this area [17,49,60] through an electronic algometer (Somedic AB, Farsta, Sweden). For this purpose, an approximate rate of 30 kPa/s will be applied with a 1 cm^2^ probe. PPTs will be bilaterally assessed. Seven points, focused on abdominal and pelvic pain [49,60], and two additional points from the lower back region [17,60], will be tested. PPTs in the abdominal wall will be assessed in the following locations: the supraumbilical point is bilaterally assessed 3 cm above the umbilical point inside the hemiclavicular line (the lateral border of each rectus muscle); the infraumbilical point is bilaterally assessed 3 cm below the umbilical point inside the hemiclavicular line. The pelvic region will be assessed using 3 points: just above the pubis and both inguinal ligaments at its midpoint in the hemiclavicular line. The lower back area will be also assessed bilaterally, at the level of the fifth lumbar vertebrae (verified by ultrasound imaging). The algometer will be placed in the paraspinal area, in the middle of halfway on the belly of the erector spinae muscle (i.e., approximately 3 cm to the right or left of the marked spinae). Additionally, the second metacarpals of both sides will be assessed as distant points to the affected area. Prior PPT assessment, assessor will ask for participants to press the switch when they first feel a change from pressure to pain. The mean of three tests (intra-examiner reliability), spaced by 30 s, will be used for the analysis. A high reliability of pressure algometry has been found (interclass correlation coefficient 0.82–0.97) [61].

In addition to algometry, participants will be asked to indicate their current levels of chronic pelvic pain, dysmenorrhea, dyspareunia, dyschezia and dysuria through a Numeric Rating Scale (NRS). It is a 11-likert scale used for subjective pain estimation. It ranges from 0 (“no pain”) to 10 (“worst imaginable pain”). Participants are asked to select the whole number that best reflects the intensity of the pain that they feel at the moment of basal and final evaluation sessions. The NRS has shown to be a reliable and valid instrument to assess pain in endometriosis patients (Pearson product moment correlation = 0.96) [62,63].

The Pain Catastrophyzing Scale (PCS) [64] will be also used to assess catastrophic thinking related to pain. This 13-item scale contains 3 subscales: helplessness, rumination and magnification. All items are rated on a 5-point scale (0–4), and therefore, scores range from 0 to 52. The PCS has been shown to have adequate to excellent internal consistency (Cronbach’s α ranged from 0.87 to 0.93) [64].

2.Muscle thickness

Images of the abdominal wall and lumbar multifidus will be obtained using an ultrasound device (Samsung HM70A echograph, Samsung LA3-16AD Linear probe) with a 12 MHz linear probe and a depth of 5 cm. The thicknesses of the external and internal oblique (OE and OI, respectively), the transversus abdominal muscles (TrA) and the lumbar multifidus, as well as the width of the lumbar multifidus, will be assessed according to a previously described methodology [60]. Patients are placed in supine position with arms lined up with the trunk, and images are gathered when patients are relaxed and at the end of the expiration movement. Three measurements of both right and left muscles diameters will be recorded with a 2-min interval between trials. Probe will be set 2.5 cm anteromedial to the mid-point between the iliac crest and the costal margin on the mid-axillary line, where the fascial boundaries between TrA, OI and OE and the superior edge of the TrA fascia lie parallel [65]. The average of three trials will be used. Ultrasound imaging has been reported to be reliable for testing muscle thickness of TrA, OI and OE (interclass correlation coefficients > 0.85, 0.65 and 0.80, respectively) [66,67].

Lumbar multifidus assessment will be performed at the fifth lumbar vertebra, marking its spinal process. For that, lordosis of prone-positioned participants will be corrected using pillows below the abdominal area. Depth of lumbar multifidus will result from the greatest perpendicular anteroposterior distance from the processes transversus to posterior layer of the lumbar fascia. Width of lumbar multifidus will be recorded as the greatest horizontal distance between the lateral aspects of the spinous process and the fascial boundary of the longissimus muscle [60]. High reliability for ultrasound evaluation of lumbar multifidus has been reported (interclass correlation coefficient = 0.88) [67].

3.Strength of the lumbopelvic region

Endurance strength of abdominal muscles will be assessed by the muscle trunk flexor endurance test that evaluates the isometric endurance of trunk flexors. For that, women are placed in supine position with hips and knees flexed at 90 degrees, feet flat approximately 30 inches from the buttocks and arms extended with hands on knees without actually touching. Patients will be instructed to separate the trunk from the stretcher to the inferior angle of the scapula and maintain this position as long as possible. Time (in seconds) will be measured [68]. Higher scores represent better performance. It has been reported that this test has high reliability (interclass correlation coefficient (ICC) > 0.95) [69].

Isometric endurance of trunk extensors will be evaluated with the muscle trunk extensor endurance test that assess the isometric endurance of back extensor muscles. Patients lying in prone position with the lower extremities stand on the bed and fixed with a strap and the trunk and upper extremities hanging on in a horizontal position with arms folded and hand in touch with the contralateral shoulder. The bed border will coincide with the anterior superior iliac spines. Women will be asked to maintain this position as long as possible. Time (in seconds) will be measured, with higher scores reflecting better performance [70]. This test has high reliability in either symptomatic and non-symptomatic low back pain individuals (ICC > 0.77) [71].

4.Lumbar spine flexibility

Flexibility of the lumbar spine will be addressed with the original Schöber test [72]. For that purpose, the physiotherapist will localize the lumbosacral junction and mark it. A second mark will be drawn 10 cm above the first one when the patients are in erect position. This distance will be measured in flexion position, with higher differences between erect and flexion position representing better flexibility.

5.Body balance

Flamingo test will be used to assess body balance. Standing on a beam with shoes removed, participants are asked to balance on the preferred leg while the free leg is flexed at the knee and the foot of this leg is close to the buttocks. Test is repeated with the contralateral leg. The number of trials needed to complete 30 s of the static position is recorded. The average of both legs was used in the analysis [73]. Lower scores reflect better balance.

6.Functional capacity

The 6-Minute Walking Test (6MWT), which showed good reliability (ICC = 0.97) [74], will be used to determine the maximum distance (in metres) that each patient can walk in 6 min. Participants will be previously familiarized with the test protocol, ‘walking as far as they can in 6 min’, increasing and decreasing the speed voluntarily. Standardized phrases of encouragement will be given by the examiner during the 6MWT. Walking pace, defined as at least one foot being weight-bearing at all times, will be monitored during the entire task. Blood pressure, heart rate, oxygen saturation and Borg Fatigue Scale will be assessed before and after the 6MWT. Higher scores represent better performance.

7.Body composition

Anthropometric measurements (including height, weight and body mass index) and body composition (skeletal muscle mass and percentage of body fat) will be recorded. An impedance meter (InBody 720; Biospace, Seoul, South Korea) will be used for these measurements, which has exhibited high reliability in previous studies [75]. Patients will be instructed to avoid eating and drinking during the hour prior to measurement. Moreover, they will be also invited to take off any wristwatch, wristband, necklace or belt during the measurement. Finally, the hour of the day of the measurement will be recorded.

8.Fatigue

Endometriosis-related fatigue will be evaluated with the Spanish version of the Piper Fatigue Scale-Revised. Although it was originally developed to assess cancer-related fatigue [76], it has been also used to assess fatigue in other musculoskeletal disorders such as heart failure [77] or gynaecological problems [78,79], including endometriosis [18,20]. This 22-item tool is grouped in 4 dimensions (behavioural/severity, affective meaning, sensory and cognitive/mood) and scores ranges from 0 to 10, with lower scores reflecting a better performance. PFS-R has high reliability (Cronbach’s α = 0.96) [76].

9.Quality of sexual life

To assess sexual function, an important aspect of the quality of life of a person, we will use the validated Female Sexual Function Index (FSFI) questionnaire [80]. It is a self-reported 19-item questionnaire that covers six dimensions, including desire, arousal, lubrication, orgasm, satisfaction and pain. Scores of each domain are calculated as the sum of the individual items contained in each domain and multiplied by the domain factor. Finally, all domain scores are summoned to calculate the overall score, ranging from 2 to 36, with higher values representing a better sexual function, considering that patients with a FSFI total score below 26 are sexually dysfunctional, whereas those scoring at or above this cut-off score are categorized as sexually functional [81]. This questionnaire has good reliability (Cronbach’s α > 0.82 for all domains) [81].

10.Gastrointestinal quality of life

The Gastrointestinal Quality of Life Index (GQLI) is a validated, 36-item, self-administered questionnaire that addresses 5 domains (digestive symptoms, physical status, emotions, social dysfunction and effects of medical treatment) [82]. Scores of individual items (0 being the worst appreciation and 4 the best appreciation) are summed in order to calculate the global score. It ranges from 0 to 144, with higher scores indicating a better gastrointestinal quality of life. It is considered that patients with a total score below 100 suffer from gastro-intestinal diseases, while healthy controls usually obtain punctuations above 126 [83]. This index has shown good reliability (Chronbach’s α > 0.90) [82] and has been previously applied to endometriosis patients [22].

11.Sleep quality

The validated Pittsburgh Sleep Quality Index (PSQI), previously used in endometriosis patients [14], will be used to address the quality and patterns of sleep of the women [84]. This 19-item instrument has moderate-high reliability (Cronbach’s α > 0.80) [85]. It is composed of seven “components” (subjective sleep quality, sleep latency, sleep duration, habitual sleep efficiency, sleep disturbances, use of sleeping medication and daytime dysfunction), each of them ranging from 0 to 3. The sum of component’s scores leads to the global score and thus ranges from 0 to 21, with higher scores indicating poor sleep quality. It has been proposed that a total score ≤ 5 indicates good sleep quality while a total score > 5 indicates poor sleep quality [84].

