Although endometriosis was described for the first time by Carl Von Rokitansky more than 150 years ago [6], little is known about the aetiology and pathogenesis of the disease and, therefore, about therapeutic options. Despite that some theories have tried to explain the development of these ectopic lesions [7], it is currently gaining recognition the endocrine-disrupting hypothesis that suggests that human exposure to synthetic chemicals with endocrine mimicking properties may be underlying the pathogenesis of endometriosis [8]. In this regard, it has been recently suggested that foetal exposure to diethylstilbesterol, a known endocrine-disrupting chemical, may underlie the development of endometriosis in adulthood [9]. In any case, an in situ chronic oxidative/inflammatory milieu originated by these ectopic lesions is frequently observed, which may lead to an altered microenvironment that includes, among others, the activation of epithelial-mesenchymal transition cell-signalling pathways [7]. Moreover, independently of their implementation site, endometriotic lesions are frequently detected to be vascularized and innervated [10,11]. The development of these nerve fibres (responsible for conveying nociceptive signals), but not the extent, location or type of endometriosis found at laparoscopy seems to be related to the severity of pain [12]. Hence, the affected women usually report dysmenorrhea (i.e., painful menstruation), dyspareunia (i.e., painful sexual intercourse), dyschezia (i.e., painful defecation), dysuria (i.e., painful urination) and, in general, chronic pelvic pain (i.e., pain perceived to originate in the pelvis lasting for longer than 6 months) [13].

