### 2.8. Data Collection

As shown in Figure 1, women will be evaluated in three moments: baseline assessment (t0), immediately after program (t1) and one year after completion of treatment (t2). Assessment will take approximately 90 min. Information gathered will be kept under lock and key. To maintain the confidentiality of personal information, a coded ID number will be assigned to each participant.

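### The pain NRS fixes a momentary reference period for four pains that the article itself defines by an event, which weakens these secondary outcomes

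*Protocol article*

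**What the plan says.** In the protocol article, section 2.4.2 (Pain), participants rate their "current levels of chronic pelvic pain, dysmenorrhea, dyspareunia, dyschezia and dysuria" on an 11-point NRS from 0 to 10. The same paragraph then fixes the reference period: the whole number chosen should reflect "the intensity of the pain that they feel at the moment of basal and final evaluation sessions". No recall period and no instruction to think of the relevant event appears anywhere in the article.

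The Introduction defines four of these pains by an event: "dysmenorrhea (i.e., painful menstruation), dyspareunia (i.e., painful sexual intercourse), dyschezia (i.e., painful defecation), dysuria (i.e., painful urination". The fifth is defined by duration: "chronic pelvic pain (i.e., pain perceived to originate in the pelvis lasting for longer than 6 months".

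On visit timing, section 2.4 states that "outcome assessment will be performed between days 2 and 10 of the menstrual cycle in women who are not using hormonal contraceptives". Section 2.8 and Table 2 place the NRS at baseline, after the programme and one year later. Section 2.9 replaces missing data with the worst-case value.

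**The concern.** An outcome item needs a reference period in which the thing measured can occur. Rating pain right now suits chronic pelvic pain, which may be present at any visit. It does not suit pain that arises only during intercourse, defecation or urination. A woman who obeys the instruction in the assessment room would give 0, or leave the item blank, however severe that pain is in her life.

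Pain intensity is a named secondary outcome, and the Introduction calls pain the most common and most disabling symptom of the disease. If several pain items sit at the floor at baseline, they have no room to improve, and a real benefit of the programme could go unseen. The missing-data rule adds to the problem. A woman for whom an event did not apply might write 0 or leave a blank, and a blank would be replaced by the worst score. The same state could then land at either end of the scale.

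**Working it through.** The article gives no figure for this point, so the check is mainly a comparison of the stated reference period with the article's own definitions.

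**Step 1: item by item.** Reference period from section 2.4.2, definitions from section 1.

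| Item | Defined by | Can a rating at the moment of the session capture it? |
|---|---|---|
| Chronic pelvic pain | duration over 6 months, no event | Yes |
| Dysmenorrhea | menstruation | Only if the visit falls in menses |
| Dyspareunia | intercourse | No |
| Dyschezia | defecation | No |
| Dysuria | urination | No |

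Four of the five items are bound to an event. Three of these fail strictly, and one depends on the visit day.

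**Step 2: dysmenorrhea and the visit window.** Inputs: the window is cycle days 2 to 10 (section 2.4), which is 10 − 2 + 1 = 9 days, and it applies only to women not using hormonal contraceptives. Bleeding length L, counted from cycle day 1, is not in the article; I assume 3 to 7 days. Visits are taken as evenly spread over the window, also an assumption.

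Window days in menses run from day 2 to day L, so the share is (L − 1)/9.

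| L (days) | Share of window in menses |
|---|---|
| 3 | 2/9 = 22% |
| 4 | 3/9 = 33% |
| 5 | 4/9 = 44% |
| 6 | 5/9 = 56% |
| 7 | 6/9 = 67% |

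At every L in this range, the window contains both bleeding and non-bleeding days. A momentary score on day 2 and one on day 9 therefore measure different things, between women and between visits of the same woman.

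**Step 3: what this does to the comparison.** Suppose a share f of women in each arm answers an event-bound item literally and scores 0 at both visits. They contribute a change of 0 whatever happened to their pain. If they are otherwise like the rest, the expected difference between arms in mean change is (1 − f) times the difference among women who rate the event. The article offers nothing from which to estimate f. For dysmenorrhea, the visit day adds variation unrelated to treatment.

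**Step 4: reach.** The primary outcome is the EHP-30 (section 2.4.1), and section 2.6 sizes the trial on its pain scale. Neither uses the NRS.

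**The case against.** The best defence is that asking for current levels of a named symptom invites a woman to rate her intercourse pain as it is these days, and that the sentence about the moment of the session merely describes the scale in general terms. The actual item wording is not reproduced. This has force against the predicted consequence: how many scores would sit at the floor depends on how women read the item, and no figure supports any particular share. It does not remove the conflict. The article goes beyond leaving a detail to the full protocol: it states a reference period, and that period does not fit four of the five items.

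Other instruments also cover part of the ground. The FSFI has a pain dimension, the GQLI includes digestive symptoms, and the EHP-30 has a pain domain. That limits the harm, but none of these is described as giving a separate score for dysmenorrhea or dysuria.

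A reader might infer more than the document supports, in three ways:

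- **That all four items cannot work.** This is too strong for dysmenorrhea, since some women will be menstruating at a day 2–10 visit.
- **That about half of paired visits differ in bleeding status.** With bleeding to day 5 and independent, evenly spread visit days, 2 × 4/9 × 5/9 = 49%. With bleeding to day 3 it is 2 × 2/9 × 7/9 = 35%. The independence is unsupported, and the figure concerns one item and only non-users of hormonal contraceptives, so I do not rest the point on it.
- **That the wording could create a spurious benefit.** Allocation is randomized, assessors are blinded, and nothing in the article ties cycle day to arm. Visit-day variation is therefore noise.

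Two neighbouring details are not substantive defects. Restricting the cycle window to non-users is a reasonable choice. The mention of only two sessions beside the NRS is loose wording, since section 2.8 and Table 2 are clear about three.

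**Conclusion.** The point holds in limited form. As written, three NRS items (dyspareunia, dyschezia, dysuria) cannot capture their target, and a fourth (dysmenorrhea) captures it only at visits that fall in menses. For women not using hormonal contraceptives, that is 22% to 67% of window days, assuming bleeding of 3 to 7 days and visits spread evenly over days 2 to 10. The likely result is floor values and added noise, and so reduced sensitivity on these secondary outcomes. How large the loss is depends on how literally women answer, which the article does not let us estimate. The chronic pelvic pain item, the primary outcome and the sample size are untouched, and no bias between arms is shown. The change is worth making because it is cheap, but the main result of the trial does not depend on it.

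**What to change.** Keep the 0–10 NRS and change the reference period:

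- Anchor each of the four items to its event over one fixed recall period, for example the worst pain during that event in the last 4 weeks. One score per item is enough.
- Add a not-applicable answer for women without the event in that period, and state in section 2.9 that it is exempt from worst-case replacement.
- Use identical wording at t0, t1 and t2.
- Keep the momentary rating for chronic pelvic pain only.

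A 4-week recall at t1 would lie within the 9-week programme and so would not reach back before treatment.

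The cost is questionnaire wording, some recall error, and fewer scored women on items where the event did not occur. No extra visit or staff is needed. If the forms in use already carry a recall period, only the text of section 2.4.2 needs correcting.

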### 2.5. Recruiting and Participant Timeline

Gynaecologists from both University hospitals (San Cecilio and Virgen de las Nieves, Granada) will provide eligible patients. Women interested in the study will receive more information about the study objectives, evaluation protocol and procedures and will sign informed consent before undertaking baseline assessment. Potential participants will need to provide a copy of laparoscopic or magnetic resonance imaging findings confirming a diagnosis of endometriosis.

